### Ethics, consent and permissions

The project was approved by Research Ethics Board of each of the participating institutions, with the caveat that the pilot trials would each have their own protocol and ethics submission. All participants provide written, informed consent at the time of enrollment in the cohort. Where deemed ethically permissible, we also collect limited information from eligible individuals who refuse participation in the study in order to estimate selection bias. The local research ethics board at one center did not approve the collection of information from refusers. For the intervention studies that are recruited through telephone or email contact and are delivered only through the Internet, no additional visit is needed. We obtained ethics approval for these intervention studies only from the center from which the study was going to be conducted, after confirmation that this approach was in compliance with the national regulatory framework in Canada.

The informed consent document stipulated that any clinical results of importance for the participant’s medical care would be provided to their physician. Most blood tests are clinically indicated and are reviewed as part of routine care. For the information collected on the questionnaires, in collaboration with the site principal investigators, we developed a list of “red flags” to identify participants who may be in serious distress. The “red flags” pertain to issues of mood, pain and quality of life, as those were considered important to medical care. On a monthly basis, answers to selected questions are extracted from the database and the participants’ physicians are alerted to the presence of worrisome self-reports.

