Although the burden of poor brain health in HIV in Canada is unknown, it is likely to be high. Recent studies in other developed countries, using comprehensive neuropsychological assessment, report a prevalence of (primarily mild) HIV-associated neurocognitive disorders (HAND) of 30–50 % [9, 10]. Even higher rates have been documented in those over the age of 50, a rapidly expanding group at the frontier of existing knowledge about the combined effects of aging and longstanding HIV infection [11]. Depression is also common in HIV infection, with population-based prevalence of major depressive disorder estimated as high as 36 % [12]. Impaired cognition and depression, whether together or separately, strike patients in their productive years, and can affect medication adherence, occupational and social function, quality of life, and even accelerate mortality [4, 13–18]. Progress in understanding the heterogeneous, multi-factorial nature of compromised brain health in HIV requires careful clinical characterization, including of its evolution over time, accompanied by hypothesis-driven research focused on specific clinical phenotypes. Progress in predicting, treating and mitigating the impact of poor brain health requires better, practical clinical tools and evidence-based interventions specifically tailored for people living with HIV.

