### Study population

The target population is people in middle age and older, the group felt to be most at risk of both longer-term effects of HIV infection and the interaction between these and aging-related brain changes: Inclusion criteria are age ≥35, HIV+ for at least 1 year, able to communicate adequately in either French or English, and able to give written informed consent. If necessary, we will oversample patients >60 years old and women to ensure at least 100 of each are enrolled. The focus is on milder cognitive deficits, which is the area of greatest clinical uncertainty. Thus, exclusion criteria include dementia (MoCA <18) [25], or treating physician’s concern about capacity to consent, life expectancy of <3 years or other personal factor limiting the ability to participate in follow-up, non-HIV-related neurological disorder likely to affect cognition, known active CNS opportunistic infection or hepatitis C requiring Interferon-based treatment during the follow-up period, psychotic disorder, or current substance use disorder or severe substance use disorder within the past 12 months. Individuals with current or past major depressive disorder are eligible for the core project, and indeed will be the focus of one of the studies under our third aim. There are additional inclusion/exclusion criteria for individual sub-studies, described below. A brief questionnaire is used to identify characteristics of all persons approached for recruitment to determine whether non-participation introduces a selection bias into our study.

The core of the research program is the development and follow-up of a comprehensively characterized cohort of persons with HIV. The cohort is being assembled through consecutive sampling from five clinics in several large cities in Canada: Montreal, Toronto, Hamilton, and Vancouver. These clinics collectively manage thousands of patients, with diverse demographic and HIV risk profiles, most of whom are routinely followed at 3 month intervals. A total of 900 participants will be comprehensively assessed and followed longitudinally at 9 month intervals over a 3 year period (four assessments).

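### Red-flag answers meant to reveal possible serious distress are extracted once a month, so as written a flagged answer waits 0 to 31 days before extraction

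*Protocol article*

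**What the plan says.** Under Ethics, consent and permissions, the article states the purpose of the screening list: "we developed a list of “red flags” to identify participants who may be in serious distress". The site principal investigators collaborated on the list, and its items "pertain to issues of mood, pain and quality of life, as those were considered important to medical care". The operating rule follows directly: "On a monthly basis, answers to selected questions are extracted from the database and the participants’ physicians are alerted". The same section says in general terms that clinically important results will reach the participant's physician, but gives no timing for this.

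Under Data collection, participants start the questionnaires on a clinic computer, with a research assistant helping as needed, and may finish them at home. The data platform is said to offer real-time validation checks, dashboards, reporting and data extraction. None of these is linked to the red flags.

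Under Study population, the cohort comes from "consecutive sampling from five clinics in several large cities in Canada". Its patients are people "most of whom are routinely followed at 3 month intervals". On depression, "Individuals with current or past major depressive disorder are eligible for the core project".

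**The concern.** A list built to pick out people who may be in serious distress is useful only if someone reads the result in time to act. The article sets one cadence for the whole list, and that cadence is a month. It draws no line between an answer that can wait, such as long-standing pain or persistent low mood, and one that a clinician would want to know about within days.

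The population makes mood flags foreseeable. People with current major depression may enrol, and the Background describes depression as common in HIV, "with population-based prevalence of major depressive disorder estimated as high as" 36 %. Where questionnaires are finished at home, no staff member is present to notice distress.

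What is at stake is the timeliness of a safety step. Once the study has collected an answer that its own list marks as worrying, an avoidable wait before anyone looks at it works against the purpose of the list.

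**Working it through.** The article gives a frequency and no waiting time, so there is no stated figure to reproduce. The wait follows from the frequency.

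**Inputs**
- Extraction once per calendar month (Ethics, consent and permissions).
- Month lengths *d* in a 365-day year: seven of 31 days, four of 30 and one of 28.
- Assumption: answers arrive evenly over the year. The article does not say so.

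**Wait from answer to extraction under the monthly rule**
- Range: 0 to 31 days, or 0 to 28 in the shortest month.
- Mean = Σd² / (2 × Σd). Here Σd² = 7 × 961 + 4 × 900 + 784 = 11,111 and Σd = 365, so the mean is 11,111 / 730 = 15.2 days.
- Share waiting more than 7 days = Σ(d − 7) / 365 = (365 − 84) / 365 = 281 / 365 = 77%.
- Share waiting more than 14 days = (365 − 168) / 365 = 197 / 365 = 54%.

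**Alternatives, measured to the same point**
- Weekly run: 0 to 7 days, mean 7 / 2 = 3.5 days. This is 15.2 − 3.5 = 11.7 days sooner on average.
- Review on the next working day: lags for answers given Monday to Sunday are 1, 1, 1, 1, 3, 2 and 1 days. The mean is 10 / 7 = 1.4 days and the longest is 3 days, more over public holidays. This is 15.2 − 1.4 = 13.8 days sooner on average.

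| Cadence | Longest wait (days) | Mean wait (days) |
|---|---|---|
| Monthly, as stated | 31 | 15.2 |
| Weekly | 7 | 3.5 |
| Next working day | 3 (longer over holidays) | 1.4 |

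All three rows stop at extraction or review. The time from there to the physician alert is not stated and would be added to each.

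**Whether another described route shortens the wait**
- The general promise to pass on important clinical results has no timing. For questionnaire answers, the mechanism that the same section gives is the monthly extraction.
- The research assistant's help is given as needed and is not described as screening for red flags.
- Routine visits are about every 3 months for most patients. The monthly alert will therefore usually come before the next visit, and usual care would often not catch a flag sooner.

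**What cannot be computed**
- The flag items, thresholds and flag rate are not given, so neither the number of people affected nor the number of urgent flags can be derived.

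**The case against.** The strongest reply is that a journal article condenses the protocol. Escalation rules for single items normally sit in the full protocol or in site procedures, and their absence from an article is no defect. That stands, and it limits the point to the cadence that the article does state. A reader might infer that no faster route exists; the article describes none, but it does not exclude one.

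A second reply is that urgency is assumed. This also stands in part. The article says that flagged participants may be in serious distress and does not call any flag an emergency. The constructs in Table 1 include depression, anxiety, stress, apathy, pain and quality of life, and no suicidality or crisis item is named. A reader might infer that answers about self-harm lie unread for a month, but nothing in the article supports that. For persistent low mood or chronic pain, a monthly alert may well be enough.

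A third reply is context. The list was developed with the site principal investigators, the institutions' ethics boards approved the project (approval of this cadence in particular is not mentioned), and questionnaires begin in the clinic with staff at hand. The monthly alert adds to usual care. All of this is fair and argues for a modest label. It does not explain why one cadence should serve every flag.

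Finally, the 77% and 54% are properties of any monthly cycle under even arrival. They measure delay and say nothing about harm.

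**Conclusion.** The point holds in a narrow form. The article states one monthly extraction for answers intended to find people who may be in serious distress. As written, a flagged answer waits 0 to 31 days, on average about 15, before extraction, plus an unstated time to the alert. The range follows from the word monthly; the mean and the shares also need even arrival. The article describes no faster tier for urgent answers.

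Two further readings should be resisted:
- The article does not contradict itself. The real-time functions under Data collection are data validation checks and were never presented as distress alerts.
- The 36 % in the Background is the high end of the estimated prevalence of major depressive disorder. It is neither a flag rate nor a ceiling on one, because the flags also cover pain and quality of life.

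This is a cheap improvement, on patient safety only. No endpoint, estimate or error rate is touched.

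**What to change.** 1. Have the site investigators mark which of the existing red flags are urgent.
2. For those flags, run the existing extraction or report each working day, or at least weekly, and alert the participant's physician promptly.
3. Keep the monthly run for the remaining flags and as a back-up check.
4. If the full protocol or site procedures already provide a faster route for urgent answers, one sentence in this section saying so is enough.

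**Cost.** The list, the platform's reporting functions and a research assistant at each site already exist, so no new staff or visits are needed. The added time is probably modest, but it cannot be quantified because the article gives neither a flag rate nor the minutes that a flag takes. For scale, 900 participants × 4 assessments = 3,600 questionnaire rounds, or 3,600 / 5 = 720 per clinic if the five clinics contribute equally. Only rounds with an urgent flag would need prompt follow-up, and physicians are already to be alerted to the same flags under the monthly rule.

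The sites would also need cover for absences and would take on a duty to respond. As the study is under way, an ethics amendment at the participating sites is probably needed. Whether the platform can report at the level of single items should be checked first, because the article lists only general reporting functions.

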## Discussion

This novel design, cohort multiple randomized controlled trials, uses the strength of a large, epidemiologically designed, observational study to provide a representative sample that can be characterized prospectively to answer questions about the evolution of outcomes of interest. In addition, sub-groups of the sample are identified for whom pilot testing of specific personalized interventions would provide pragmatic evidence for feasibility, effectiveness, and acceptability to patients. The study will also provide a powerful platform for validating novel measurement approaches and estimates of the burden and heterogeneity of cognitive deficits over time, and will support hypothesis-driven research on mechanisms.

The findings from this work will be rigorous and the extent of their generalizability can be estimated. We expect the results will apply to similar populations cared for in specialized HIV clinics in Canada and the developed world more generally, at least. We believe this whole person approach to brain health, emphasizing evolution over time, and testing non-pharmacological interventions, will yield both conceptual advances and practical, clinically-relevant information applicable in the day-to-day management of brain health in HIV. We anticipate making this rich dataset publically available at the completion of the study, following publication of the primary research findings.

This study is also an example of interdisciplinary and multi-site team science, enabled by funding from the Canadian Institutes of Health Research that was earmarked to promote the development of new teams to address emerging co-morbidities in HIV. We have included community partners as part of our team. They have been involved from the beginning, endorsing the relevance of addressing cognitive concerns. These individuals have also been invaluable for informing methods of data collection and championing the study in the community.

Chronic HIV infection poses complex challenges that are likely exacerbated by aging and the accrual of co-morbidities, and likely affect brain health through multiple paths. This project takes a multi-pronged approach to measuring cognition and mental health concerns, understanding the basis of differences in cognitive ability, and assessing potential interventions. We apply a novel approach, the cohort multiple randomized controlled trials design. Since a pivotal paper on this method was published in 2009 [24], only a handful of studies have proposed this design [44–48]. This will be the first study to use this design to test multiple interventions.

## Abbreviations

ARV: anti-retroviral
B-CAM: brief cognitive ability measure
CD4: cluster differentiation 4
CI: confidence interval
CNS: central nervous system
D-KEFS: Delis-Kaplan executive function system
GBTA: group-based trajectory analysis
GEE: generalized estimating equations
HAART: highly active antiretroviral therapy
HAND: HIV-associated neurocognitive disorders
HIV: human immunodeficiency virus
IQ: intelligence quotient
MCI: mild cognitive impairment
MUHC: McGill University Health Centre
OR: odds ratio
PDQ: perceived deficits questionnaire
QOL: quality of life
SEM: structural equation modeling
WAIS-IV: Wechsler adult intelligence scale-IV (WAIS-IV)
WMS-III: Wechsler memory scale-III (WMS-III)
